##### Secondary (Patient) Outcomes

For assessing the morbidity of musculoskeletal injuries, the validated 10-item TEFS will be used at baseline and the 10-item TOMS will be used at 90 days [30]. The mean difference in the TEFS and TOMS will be compared between the intervention and control groups using the 2-sample *t* test. Further, the TOMS will be dichotomized into favorable (TOMS ≥ TEFS) and unfavorable (TOMS < TEFS) outcomes in accordance with previous studies [30]. The difference in these proportions between the intervention and control groups will be compared using the adjusted chi-square test if the expected count is >5 or the Fisher exact test at 95% CI otherwise.

Further, subgroup analyses will be performed to determine and control for factors that could be associated with an unfavorable TOMS, using individual-level between-within mixed effects regression models, which inherently overcome the effect of smaller clusters and permit adjustment for covariates in a single stage, assuming equal allocation. The fixed effect variables will be the treatment arms (intervention vs control) as the unit of analysis, with the odds ratios (ORs) and their corresponding 95% CIs as direct estimates of the effect size. The covariates will include age, sex, education level, occupation, employment status, marital status, commute distance, road user category, injury severity score based on the KTS, presence or absence of fracture, nature of fracture if present, number of serious injuries, and treatment (surgical vs conservative).

For assessing the morbidity of neurological injuries, the validated GOS will be used at 90 days after injury. The mean difference in the GOS score will be compared between the intervention and control groups using the 2-sample *t* test. Further, the GOS score will be dichotomized into favorable (GOS score of 4 or 5) and unfavorable (GOS score of 3, 2, or 1) outcomes in accordance with previous studies [7]. The difference in proportions between the intervention and control groups will be compared using the adjusted chi-square test if the expected count is >5 or the Fisher exact test at 95% CI otherwise.

For all-cause mortality, the difference in proportions of all deaths at 90 days after injury will be compared between the intervention and control groups using the chi-square test if the expected count is >5 or the Fisher exact test at 95% CI otherwise. Lastly, we will conduct subgroup analyses to determine and control for factors associated with all-cause mortality using individual- and cluster-level between-within mixed effects regression models. The covariates will include age, sex, injury mechanism (including helmet use), mode of arrival, prehospital interval, referral decision to hospital discharge interval (dichotomized as ≤1 hour or >1 hour), prehospital first aid status, comorbidities, injury severity score based on the GCS at baseline, multiplicity of injuries, head and brain CT-based diagnosis, and neurosurgical intervention.

These variables have been found to influence outcomes following neurological trauma in previous studies [7]. All variables will be analyzed for confounding and effect modification using Mantel-Haenszel statistics to probe necessary interaction terms. Variables with *P* values of ≤0.2 in the bivariate analysis will be included in the multivariate analysis. The median (IQR) of the time to the event, that is, from the accident to death (in days), will be stratified by treatment arm, and the difference will be compared using the Wilcoxon 2-sample test. All analyses will be performed using Stata 15.0, and where appropriate, graphics, such as box plots, will be used to visualize the data.

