### Sample Size

To estimate the sample size, we used the open-source R Shiny application for cluster randomized controlled trials with a parallel design and discrete time decay correlation structures for multiple periods [36] available at [37]. Further, we assumed *t*-distribution due to plans for small sample corrections at the analysis stage in accordance with the report by Rutterford et al [38]. The study was approved for 4 years, but the core research team foresaw it feasible to actively collect data for a period of 3 years considering university semester breaks, public holidays, and unexpected events, such as COVID-19–related interruptions, which led to suspension of the trial for 12 months from March 2020 to March 2021. The 3 years (36 months) would yield 12 study periods given the planned training of cohorts of medical students on a 3-monthly basis in accordance with the average duration of internship deployment by the Ugandan Ministry of Health (1-5 months) and the average duration of surgery clinical rotation for university medical students (2 months).

Fixing the study power at 80% for a parallel cluster randomized trial with different cross-sections, considering a discrete time decay period of every 3 months for a total of 12 periods, and assuming correlations to decay with each period, we explored the minimum number of patient participants (cluster size) required per period using the R Shiny application [36]. Assuming a significance level of .05, a within-period intraclass correlation coefficient (ICC) of 0.02 (lower extreme: 0.01, upper extreme: 0.05), and a cluster autocorrelation coefficient (CAC) (ratio of between-period ICC to within-period ICC) of 0.8; allowing for varying cluster sizes with a coefficient of variation of 0.5; and considering a mean difference of 1.02 hours in prehospital transfer time and a pooled standard deviation of 1.64 hours as continuous outcomes reported in a previous observational study from the United States [39], the upper ICC and base CAC plateaued between 5 and 10 participants (Figure 2).

Considering a maximum of 10 participants per cluster period, an 80% power could be attained (Figure 3) and could be met with a total of 3 clusters per arm (Figure 4). This indicates a total of 6 study centers (clusters) drawn from a pool of 17, which reasonably represents 35.3% of Uganda’s regional referral hospitals.

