Further, the tools are recognized for their high interrater reliability, sensitivity to change, and ability to be used as continuous or categorical variables in validation studies [28,29,43,44]. The baseline TEFS, GCS score, and KTS will be added as covariates whose interaction and confounding will be assessed and controlled since the inclusion of baseline values of outcomes as covariates is arguably one of the strongest factors to reduce ICC estimates [45]. The difference in distribution of baseline characteristics will be compared using means (SDs), medians (IQRs), and ranges for quantitative data; otherwise, frequencies and percentages will be used for categorical variables. All data collection forms for this trial and detailed definitions of assessment tools for patient and trainee participants are available in Multimedia Appendix 5 and Multimedia Appendix 6, respectively.

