### Study Limitations

Despite the strengths of this trial, we anticipate some limitations. First, while the authors are ambitious to assume that the study centers are homogeneous, the heterogeneity among the 6 participating regional referral hospitals could cause bias and affect study estimates. Further, the relatively smaller number of clusters could affect the power of the study. However, randomization of 6 out of the 17 trauma centers is within the ethical constraints as this sample already represents 35.3% of Uganda’s regional referral hospitals. To overcome the statistical power bias limitation, the sample size is inflated for individual randomization to cater to the design effects in accordance with the report by Hooper et al [45]. Moreover, we plan to use mixed effects regression models, which permit adjustments for covariates at both the cluster and individual levels in a single-stage approach, and plan to use the *t* test, which is robust in terms of normality deviations. According to Borhan et al [52], mixed effects models are deemed suitable for smaller clusters in situations where the primary outcomes are continuous, which is the case in this trial. Further, we hope that the ancillary studies with mixed methods will add value to the overall interpretation of the trial results by providing data from individuals outside the health sector, such as traffic law enforcement professionals.

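### The full TOMS score gets only an unadjusted, unclustered t test, while the only clustered, adjusted TOMS model spelled out is for the binary TOMS < TEFS outcome

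*Protocol article*

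**What the plan says.** The Secondary (Patient) Outcomes section gives three analyses for musculoskeletal injury, in this order:

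1. The TEFS and TOMS mean difference is compared between arms by a 2-sample t test. No hospital term or covariate is named.
2. Then "the TOMS will be dichotomized into favorable (TOMS ≥ TEFS) and unfavorable (TOMS < TEFS) outcomes", with the proportions compared by an adjusted chi-square test or Fisher's exact test.
3. An individual-level between-within mixed model for factors associated with an unfavorable TOMS, introduced as a subgroup analysis. It has treatment arm as fixed effect and a long covariate list, "with the odds ratios (ORs) and their corresponding 95% CIs as direct estimates of the effect size".

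Elsewhere the article is more general. The Abstract (Methods) promises mixed models reporting absolute or relative differences with 95% CIs. The Outcomes section says outcomes are measured as final values and compared by mixed models at individual and cluster level. Plans for Assessment and Collection of Outcomes makes baseline TEFS a covariate and credits the tools with the "ability to be used as continuous or categorical variables in validation studies". Sample Size foresees small-sample corrections at the analysis stage.

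**The concern.** The full score and the suitable model are never brought together. The t test keeps the whole scale but treats patients within a hospital as independent, so its nominal 5% level does not hold if hospitals differ. The mixed model handles hospitals and covariates, but it is fitted to an outcome that counts a patient just below expectation the same as one far below.

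The general statements would lead a reader to expect a linear mixed model for TOMS adjusted for TEFS. The section that specifies the analyses does not write one, and TEFS is absent from its covariate list for the TOMS model. At stake is the precision and validity of the orthopedic morbidity result, which rests on a subset of patients in six hospitals.

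**Working it through.** **The plan's own figures.** The inputs are "Assuming a significance level of .05", "Fixing the study power at 80% for a parallel cluster randomized trial", "a within-period intraclass correlation coefficient (ICC) of 0.02 (lower extreme: 0.01, upper extreme: 0.05") and "a mean difference of 1.02 hours in prehospital transfer time and a pooled standard deviation of 1.64 hours". The sample size reproduces: 10 × 12 × 3 × 2 = 720; 720 × (1 + 9 × 0.02) = 849.6, rounded to 850; 850 × 1.18 = 1003, stated as about 168 per hospital. All of this concerns prehospital time. Nothing is sized for TOMS.

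**Assumed inputs for TOMS.** The article cites a Ugandan series with 30.9% musculoskeletal injuries: 168 × 0.309 ≈ 52 per hospital, and 52 × 0.82 ≈ 43 after 18% loss. I assume a normal score with SD 1, two-sided 5%, 3 hospitals per arm and 4 df, and I borrow the ICC from the sample size section. The article gives no TOMS SD, effect or unfavorable rate.

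**1. The t test as named.** With m = 43, the design effect is 1 + (m − 1) × ICC. At ICC 0.02 it is 1 + 42 × 0.02 = 1.84. The actual type I error is about 2Φ(−1.96/√1.84) ≈ 15%. At ICC 0.01 (design effect 1.42) it is about 10%, and at ICC 0.05 (3.10) about 27%. Simulation of the t test agrees.

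**2. Clustered analysis of the full score.** SE = √[2 × (1 + (m − 1) × ICC) / (3m)] = √(2 × 1.84 / 129) = 0.169 SD. For 80% power, a noncentral t with 4 df needs a noncentrality of 3.76. The shift is 3.76 × 0.169 = 0.635 SD.

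**3. The same shift after the cut.** Let u be the control unfavorable proportion and u₁ = Φ(Φ⁻¹(u) − 0.635). The binary ICC comes from the bivariate normal (for controls 0.0127, 0.0121 and 0.0108 at u = 0.50, 0.35 and 0.25). Each arm's variance is p(1 − p)[1 + 42 × ICC_bin]/129.

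| u | u₁ | SE | (u − u₁)/SE | Power |
|---|---|---|---|---|
| 0.50 | 0.263 | 0.0719 | 3.30 | 70% |
| 0.35 | 0.154 | 0.0635 | 3.09 | 64% |
| 0.25 | 0.095 | 0.0545 | 2.84 | 58% |

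**4. Sensitivity.**
- With 52 per hospital and ICC 0.02: 71%, 66% and 59%.
- With 43 per hospital: 67%, 61% and 55% at ICC 0.01; 74%, 68% and 60% at ICC 0.05.
- With 43 per hospital and ICC 0.02: a 10% unfavorable rate gives 38%; rates of 65% and 75% give 71% and 69%.
- The plan's correlation decay (CAC 0.8 over 12 periods) multiplies the ICC by an average of (1/144) × Σ 0.8^|i−j| = 0.49. An ICC of 0.02 then acts like about 0.01, so the ICC 0.01 figures apply.

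**The case against.** The strongest reply is that the score is not abandoned: the mean comparison comes first and the split second. That is correct. A reader might infer that the trial's continuous effect estimate itself loses power, or that a shift crossing no threshold would simply be missed. The article does not support this, because the computed loss belongs to the binary model alone. What remains is that the mean comparison, as named, is not valid for clustered data.

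A reader might also infer that the odds ratio is the main musculoskeletal result. The article does not say so, and introduces that model as a subgroup or risk-factor analysis. Its wording about direct estimates of effect size is ambiguous but does not give the model that rank.

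It is tempting to read Study Limitations as a contradiction, since it says "mixed effects models are deemed suitable for smaller clusters in situations where the primary outcomes are continuous". That sentence concerns the primary time intervals and does not bear on a binary secondary analysis.

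The cut is not arbitrary either. It asks whether each patient's own expectation was met, which is how Participant Timeline describes the score.

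The general statements on mixed models, absolute differences and TEFS already point toward the remedy, and an appendix that is not shown lists analysis metrics. This limits the point to reconciling the section with those statements. It does not remove it, because the section states a specific and weaker method.

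Finally, the calculation cuts one normal variable (the score relative to expectation), while the remedy models TOMS with TEFS as covariate. The exact gain from the remedy was not computed.

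**Conclusion.** The point holds as a mismatch between the specified TOMS analyses and the article's own general plan. The full score is tied to a test that ignores hospitals, and the clustered, adjusted model is tied to the binary outcome.

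Under the stated assumptions (normal score, 43 patients per hospital, ICC 0.02, 25% to 50% of controls unfavorable), the binary model has 58% to 70% power against 80%, a loss of about 10 to 22 points. At the same ICC, the t test's type I error would be about 15% instead of 5%. Both figures move with inputs that the article does not give, so they show direction and rough size only. TOMS is secondary and the article declines to size it, so no stated power is missed.

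**What to change.** In Secondary (Patient) Outcomes, replace the t test on the score with a linear mixed model for the 90-day TOMS:

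- arm as fixed effect and hospital as random effect;
- baseline TEFS as covariate, since the plan judges TOMS against each patient's own expectation;
- the planned pre-injury and injury covariates;
- the small-sample correction foreseen in Sample Size.

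Report the adjusted mean difference with 95% CI as the main musculoskeletal result. Keep the TOMS ≥ TEFS split and its odds ratio as supporting, and align the wording with the Abstract, Outcomes and data collection sections.

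The cost is analysis wording only, because TOMS and TEFS are already planned data. Follow-up had ended and analysis was planned for Spring 2024, so the model should be fixed before outcomes are compared by arm. One small downside is that a mean difference is less easily read than a proportion, which the retained split covers.

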These variables align well with the proposed global surgery framework to improve national surgical, obstetric, and anesthesia care provider plans [34]. In addition, the variables expand on outcomes for trauma-informed interventions [35]. All outcomes will be measured as final values but will be discussed in relation to the baseline established in our prior feasibility studies [7,30]. The comparisons of outcomes will be made at both individual and cluster levels, using mixed effects regression models.

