**Figure 4 figure4:**
[figure not shown]
Three clusters per arm meeting the minimum required power of 0.8 for 12 periods. CAC: cluster autocorrelation coefficient; ICC: intraclass correlation coefficient.

The sample required per arm is calculated as follows: 10 participants per cluster period multiplied by 12 cluster periods multiplied by 3 clusters, yielding a total of 360 participants. The total sample required for 2 arms would be 720. However, we inflated the sample and variance to cater to the clustering design effect based on the assumption that this increases the statistical power in accordance with the repost by Hemming et al [36]. Thus, the derived sample size (s) is calculated using the following formula:

s = n (1 + [m − 1] ρ) **(1)**

where s is the required sample size, m is the cluster size per period (ie, 10), and ρ is the within-period ICC (0.02).

This formula yields a total of 850 participants.

We will add a rate of loss to follow-up of 18% assuming the worst scenario based on our previous dropout rate of 9% in a feasibility study [7]. Therefore, the final sample will include approximately 1003 participants. Assuming an equal allocation ratio of 1:1, there will be 502 participants per arm and about 168 individuals per cluster. This sample is deemed feasible considering the high trauma burden in Uganda. According to a study at one of the Ugandan rural regional referral hospitals, a total of 900 motorcycle accident–related injuries were recorded during a 3-year period, of which 30.9% (278/900) and 15.8% (142/900) of patients sustained musculoskeletal and neurological injuries, respectively [8]. We will not compute sample sizes for each individual secondary outcome as previous studies have not reported any difference in mortality [40].

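### Ninety-day GOS is compared by an individual-level t test on means and a 4-5 versus 1-3 split; an ordinal mixed model would suit it better, with a modest gain over the t test

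*Protocol article*

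**What the plan says.** Neurological morbidity is a secondary outcome, and the article states that "the validated GOS will be used at 90 days after injury". Under Secondary (Patient) Outcomes it fixes two comparisons:

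- Means: "The mean difference in the GOS score will be compared between the intervention and control groups", by a 2-sample t test.
- A split: "the GOS score will be dichotomized into favorable (GOS score of 4 or 5) and unfavorable (GOS score of 3, 2, or 1) outcomes". For this, "The difference in proportions between the intervention and control groups will be compared using the adjusted chi-square test if the expected count is >5", with the Fisher exact test otherwise.

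Neither is called the main GOS analysis. The same section names mixed effects models for an unfavorable TOMS and for mortality, but none for GOS. The Outcomes section is more general: "The comparisons of outcomes will be made at both individual and cluster levels, using mixed effects regression models".

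The Sample Size section cites one hospital's record, in which 142 of 900 motorcycle injuries (15.8%) were neurological. It sets a final sample of about 1003 and computes no sample size for secondary outcomes.

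**The concern.** GOS is an ordered scale with five levels. A difference in means counts the step from 1 to 2 the same as the step from 4 to 5. If level 1 is death, as the scale is usually defined (the article does not spell this out), that puts the step between death and survival on a par with a step between two grades of recovery. A mean difference also does not show which outcomes moved.

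The split has a plain clinical reading but sees only movement across the 3/4 boundary.

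As worded, the t test treats patients as independent although hospitals were randomized. The article does not explain what the chi-square test is adjusted for, so the clustering criticism is certain for the t test and open for the split.

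At stake are precision in a small subgroup, an estimate that can be read, and a valid error rate for one secondary outcome.

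**Working it through.** **Size of the subgroup.** The article's total reproduces: 10 × 12 × 3 × 2 = 720; 720 × (1 + 9 × 0.02) = 849.6; 849.6 × 1.18 = 1002.5, or about 1003. Applying the single-hospital rate, 1003 × 142/900 = 158. After the plan's 18% loss, 158 × 0.82 = 130, or 65 per arm and about 22 per hospital (26 before loss).

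**Information without clustering.** The article gives no GOS distribution, so four are assumed. Let p be the proportions at the five levels, F the cumulative proportions at the four cuts, and q the proportion at 4-5. For a small common shift in log odds, the information per patient is proportional to:

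- ordinal (proportional odds): (1 − Σp³)/3
- split: q(1 − q)
- difference in means: [ΣF(1 − F)]² / Var(GOS)

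First row worked: Σp³ = 0.4254, so ordinal = 0.5746/3 = 0.1915. Split = 0.90 × 0.10 = 0.0900. F = 0.05, 0.06, 0.10, 0.25, so ΣF(1 − F) = 0.0475 + 0.0564 + 0.0900 + 0.1875 = 0.3814; Var = 0.9884; means = 0.3814²/0.9884 = 0.1472.

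| GOS 1/2/3/4/5, % | Ordinal | Split | Means | Loss, split | Loss, t test |
|---|---|---|---|---|---|
| 5/1/4/15/75 | 0.1915 | 0.0900 | 0.1472 | 53% | 23% |
| 10/2/8/20/60 | 0.2582 | 0.1600 | 0.2180 | 38% | 16% |
| 20/3/12/25/40 | 0.3035 | 0.2275 | 0.2820 | 25% | 7% |
| 25/5/15/20/35 | 0.3100 | 0.2475 | 0.3012 | 20% | 3% |

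**With hospital variation.** Between-hospital variance adds the same term to each analysis, so the relative loss shrinks. Assume a latent-scale ICC ρ, so σ² = [ρ/(1 − ρ)] × π²/3. With 130 patients and 3 hospitals per arm, the variance of the log odds ratio is 4/(130 × information) + 2σ²/3. First row at ρ = 0.02: σ² = 0.0671; ordinal 0.2054, split 0.3866, means 0.2538. Losses: 1 − 0.2054/0.3866 = 46.9% and 1 − 0.2054/0.2538 = 19.1%.

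| GOS, % | Split, ρ 0.02 | Split, ρ 0.05 | t test, ρ 0.02 | t test, ρ 0.05 |
|---|---|---|---|---|
| 5/1/4/15/75 | 46.9% | 39.6% | 19.1% | 14.9% |
| 10/2/8/20/60 | 30.8% | 23.8% | 11.8% | 8.6% |
| 20/3/12/25/40 | 18.8% | 13.5% | 5.0% | 3.4% |
| 25/5/15/20/35 | 14.8% | 10.5% | 2.0% | 1.3% |

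These rows suppose that all three analyses allow for hospital.

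**Simulated power.** This used 65 per arm, a common odds ratio of 2, independent patients, 4000 runs per setting, and five assumed distributions with 40% to 90% favorable outcomes. Power was 0.33-0.60 (ordinal), 0.27-0.59 (t test) and 0.17-0.48 (split). In each setting the ordinal test led the t test by about 1 to 7 points.

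**Ignoring hospital.** If the plan's ICC range of 0.01 to 0.05 applied to GOS, the design effect 1 + (m − 1) × ICC runs from 1.21 (m = 22, ICC 0.01) to 2.25 (m = 26, ICC 0.05). A nominal 0.05 test then has a true level, 2 × [1 − Φ(1.96/√design effect)], of about 0.07 to 0.19.

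**The case against.** The t test already uses all five levels, so the plan as a whole does not throw information away. A reader might infer from the 20-53% figure that the plan wastes up to half of its neurological patients. The documents do not support that: the figure applies to the split alone, without clustering. For the test to be replaced, the loss is about 3-23%, or about 1-19% with hospital variation. This stands, and it limits the point.

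The article gives grounds for both forms. Plans for Assessment and Collection of Outcomes says, with citations, that its tools can serve as continuous or categorical variables, and the split follows earlier studies. Study Limitations calls the t test robust to non-normality. This supports using the t test, but robustness concerns the p value, and prior continuous use does not make the steps equal.

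The proportion sits beside the mean, so it would be too strong to say that the GOS result cannot be interpreted. That stands too.

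Proportional odds may fail. The article notes that earlier studies found no mortality difference; if training shifts disability but not death, the common odds ratio averages unlike effects. This is a real cost, and keeping the split only partly answers it.

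Finally, the article is condensed and refers analysis metrics to Multimedia Appendix 3, which is not shown. An unnamed main analysis is therefore not an error in itself. What can be judged is the two tests that the article fixes.

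**Conclusion.** The point holds as an improvement, not as an error of fact. The t test on mean GOS rests on equal steps and, as worded, on independent patients. That departs from the article's own promise of mixed models. The split loses more information, about 20-53% without clustering and 10-47% with it, but it is a declared convention with a clear reading.

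The gain from replacing the t test is modest. The stronger reasons are an estimate that needs no spacing assumption and an analysis that allows for hospital. The second is a benefit of modelling the clusters, not of ordinal modelling.

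The sizes rest on assumed GOS distributions, proportional odds, a latent ICC carried over from the plan's range for another outcome, and a neurological share taken from one hospital.

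**What to change.** Under Secondary (Patient) Outcomes, replace the t test by a proportional-odds mixed model of day-90 GOS with a hospital random intercept. Report the common odds ratio with its 95% CI, using a t reference on 4 df (6 hospitals minus 2 arms), and name this the main GOS analysis. Keep the 4-5 versus 1-3 proportion as supportive, analyzed with allowance for hospital. Use it, with the odds ratios at the other cuts and the lowest cut in particular, as a check on proportional odds.

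Follow-up ended in August 2023 and analysis was set for Spring 2024. The allocation codes were to be revealed to the biostatistician at the interim analysis of August 2022. The change should therefore be dated and recorded as made before the final analysis.

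The cost is wording only, with no new data. The downsides are the proportional-odds assumption and a modest gain over the t test for one secondary outcome.

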### Outcomes

This trial will examine both process measures and patient outcomes. The primary (process) outcomes of this trial will involve comparisons of (1) the time interval from the accident to hospital admission and (2) the time interval from the referral decision to hospital discharge between patients with motorcycle accident–related injuries presenting to the intervention centers and those presenting to the control centers.

The secondary (patient) outcomes of this trial will involve comparisons of (1) all-cause mortality at 90 days from the time of injury and (2) morbidity of motorcycle accident–related orthopedic and neurological injuries between patients presenting to the intervention centers and those presenting to the control centers. The morbidity of orthopedic injuries will be measured based on the Trauma Expectation Factor Score (TEFS) at admission and the Trauma Outcome Measure Score (TOMS) at 90 days as reported to outcome assessors [28]. On the other hand, for neurological injuries, the Glasgow Coma Scale (GCS) at admission and Glasgow Outcome Scale (GOS) at 90 days will be used as documented by the attending clinicians [29].

The tertiary outcomes will involve the effects of the training on provider knowledge based on pretraining and posttraining trauma-related MCQ scores and the barriers to injury care faced by providers during execution of definitive treatment. These will be determined in 2 ancillary studies that have been approved as part of this trial, and the protocols have been detailed elsewhere [25]. A summary of all outcomes and their case definitions, specific measurement variables, analysis metrics, methods of aggregation, and time points has been provided in Multimedia Appendix 3.

The patient outcomes were selected based on their validity and relevance in previous studies [7,30]. Further, level III evidence suggests that prolonged prehospital times may be associated with increased mortality among trauma patients [31]. However, it is unclear how these results relate to time-sensitive orthopedic and neurological injuries in LMICs that lack formal coordinated prehospital systems [32]. Thus, our process outcome measure variables were selected within the context of evidence-based practice. This practice stipulates that in accordance with the golden hour rule, a major trauma patient should be in the right place within 60 minutes following injury, otherwise there is a risk of mortality or morbidity [33].

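### The mortality model adjusts for both primary outcomes and for care that training may change, and the TOMS model for type of treatment, so their arm effects are not the total effect of training

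*Protocol article*

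**What the plan says.** The Outcomes section defines the primary outcomes as "the time interval from the accident to hospital admission and (2) the time interval from the referral decision to hospital discharge".

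Under Secondary (Patient) Outcomes, the mixed model for all-cause mortality lists among its covariates "mode of arrival, prehospital interval, referral decision to hospital discharge interval", the last of these cut at 1 hour, followed by prehospital first aid. The same list ends with "head and brain CT-based diagnosis, and neurosurgical intervention". Variables with P "values of ≤0.2 in the bivariate analysis will be included in the multivariate analysis".

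The mixed model for an unfavourable TOMS has a different list. It contains neither interval and ends with "number of serious injuries, and treatment (surgical vs conservative" as its one variable for care given. The TOMS paragraph also says that the arm odds ratios from its model estimate the size of the effect.

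Both models are introduced as subgroup analyses meant to identify and control for associated factors. However, the Abstract says that mixed models will supply the reported differences with confidence intervals, and the Outcomes section says that outcomes will be compared with mixed models at individual and cluster level. Crude comparisons are also planned: a chi-square or Fisher test for mortality, and a t test and an adjusted chi-square or Fisher test for TOMS.

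**The concern.** The protocol gives its own causal account. The Intervention Description has trained police and trainees coordinating evacuation, referral and arrival. The Outcomes section justifies the interval outcomes by a possible link between long prehospital times and death. On that account, training shortens the intervals and changes early care, and this in turn lowers mortality and morbidity.

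Variables on that path follow from allocation and are not confounders of it. A model that holds them fixed asks what training does apart from faster and better coordinated care, which is not the stated secondary objective. A real benefit could be reported as little or no effect. If an unmeasured factor affects both the interval and death, conditioning on the interval also adds bias that randomisation had excluded. The P≤0.2 rule then lets the data decide which of these variables enter, and so which effect is estimated.

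**Working it through.** **Step 1: covariate lists against the outcome definitions**

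| Covariate | Mortality model | TOMS model | Why training may change it |
|---|---|---|---|
| Prehospital interval | yes | no | First primary outcome (read as accident to admission) |
| Referral decision to discharge interval, cut at 1 hour | yes | no | Second primary outcome, by name |
| Mode of arrival | yes | no | Evacuation is coordinated by trained teams |
| Prehospital first aid | yes | no | Trained officers attend the scene |
| Neurosurgical intervention | yes | no | Care given after allocation |
| Surgical versus conservative treatment | no | yes | Care given after allocation |

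Commute distance, in the TOMS list, is a distance and not the interval.

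**Step 2: the plan's own figures**

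10 × 12 × 3 × 2 = 720. Then 720 × (1 + 9 × 0.02) = 849.6, or 850. Then 850 × 1.18 = 1003. The stated sample size is reproduced. The Sample Size section computes none for the secondary outcomes, so removing covariates from their models changes no stated figure.

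**Step 3: illustration of the size of the problem**

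From the Sample Size section: interval shortened by 1.02 hours, SD 1.64 hours. Assumed, not in the protocol: total odds ratio for death about 0.70, mean control interval 3 hours, logit intercept −2.5 (deaths came out at about 7% to 10%), and the share s of the effect that runs through the interval.

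- Interval = 3 − 1.02 × arm + 1.64 × standard normal noise.
- Logit(death) = −2.5 + b × (interval − 3) + (1 − s) × ln(0.70) × arm, with b = s × ln(0.70)/(−1.02). For s = 1, b = 0.357/1.02 = 0.350 per hour.
- In the second scenario, an unmeasured standard normal factor has correlation 0.5 with the interval and adds 0.7 per unit to the logit.
- 400,000 simulated patients per run. Clustering is ignored, because the question is bias and not precision.

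| Share s | OR without interval | OR with interval | Common cause: OR without interval | Common cause: OR with interval |
|---|---|---|---|---|
| 25% | 0.698 | 0.761 | 0.730 | 0.975 |
| 50% | 0.702 | 0.840 | 0.715 | 1.034 |
| 75% | 0.702 | 0.909 | 0.727 | 1.135 |
| 100% | 0.706 | 0.997 | 0.733 | 1.234 |

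The third column can be checked by hand. Once the interval is held fixed, the remaining odds ratio is 0.70 to the power (1 − s): 0.765, 0.837, 0.915 and 1.00.

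**Step 4: the referral interval**

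The interval needs a referral decision, and the protocol records need for referral as a variable, so some patients will have no value. The stated coding has only two levels, up to 1 hour and above. Without a category for non-referred patients, a complete-case model containing this variable would drop them.

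**The case against.** Three arguments have weight. First, the mortality paragraph speaks of factors associated with death, which reads at least partly as a prognostic model, and such a model may contain mediators. Its role is therefore ambiguous. But the Abstract and the Outcomes section name mixed models as the comparison of outcomes, and no other mixed model for mortality is described.

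Second, the crude comparisons do not condition on any of these variables, so the plan does not lose the total effect altogether. This stands. It does not settle the matter, because the mortality chi-square or Fisher test carries no stated allowance for clustering in six hospitals. The mixed model is the only described mortality comparison that does.

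Third, only secondary outcomes, for which no sample size was computed, are affected.

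Some stronger readings are tempting but not supported:

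- A reader might infer that both models adjust for the primary outcomes. The TOMS list contains neither.
- A reader might carry the statement on odds ratios as effect estimates over to mortality. It belongs to the TOMS paragraph.
- A reader might infer that adjustment removes the whole effect. That needs full mediation. In general only the mediated part goes, and each variable enters only if it passes the screen.
- A reader might take it that the screen singles out mediators. It keeps any variable associated with the outcome, such as age or comorbidity.
- A reader might take the loss of non-referred patients as certain. It depends on coding that the protocol does not state.

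**Conclusion.** The point holds for the mortality model, which lists both primary outcomes and three further variables that training may change. It holds more narrowly for the TOMS model, through surgical versus conservative treatment alone. Neither adjusted arm effect can be read as the total effect of training.

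The shift depends on how much of the effect is mediated, which the documents do not give. From a total odds ratio of about 0.70, it runs from slight (0.76 at 25%) to complete (1.00 at 100%). With the assumed common cause, the adjusted value lies between 0.98 and 1.23, so a benefit could even appear as harm. These figures illustrate direction and range and do not forecast this trial's result. They rest on the assumed total odds ratio, death rate and strength of the common cause, and on reading the prehospital interval as accident to admission.

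**What to change.** - Estimate the arm effect on mortality and on TOMS in a mixed model with hospital as a random effect, period, and a prespecified set of covariates that training cannot change, for example age, sex, road user category, injury mechanism, helmet use, comorbidities and commute distance. Hospital cannot be a fixed factor: each hospital belongs to one arm, so it would be collinear with arm.
- Remove the two intervals, mode of arrival, first aid, surgical versus conservative treatment and neurosurgical intervention from these models, and drop the P≤0.2 rule for them.
- Make the model without arrival GCS and KTS the main one, and report the version with them as a sensitivity analysis, since both are measured after prehospital care. Align the statement under Plans for Assessment and Collection of Outcomes that adds these scores as covariates.
- Label any model with intervals or treatments as a prognostic or mediation analysis. If the referral interval is used there, state how non-referred patients are coded.

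The cost is analysis wording only. The variables are already in the planned data collection, and the protocol places the analysis after the last follow-up, in Spring 2024.
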